### Primary and secondary endpoints

2.4

The primary endpoint is the rate of cardiac implantable electronic device implementation. The secondary endpoints are shown in Table 4. Other significant factors besides the primary endpoint include the incidence of VT/VF, the presence of sudden death, all‐cause mortality, and HF hospitalization, as well as other variables. We will gather standard clinical background information, each patient's Clinical Frailty Scale score, laboratory test results (including measures of nutritional status), and serial changes, which will also serve as secondary endpoints.

**TABLE 4 joa313028-tbl-0004:** Primary and secondary endpoints.

Primary endpoint	
Rate of cardiac electronic device implantation (ICD, CRT‐D, WCD, CRT‐P, or None)	
Secondary endpoints	
Occurrence of any of the following	
1. VT/VF and Sudden death^a^	
2. Death from any cause	
3. Cardiovascular events (stroke/TIA or systemic embolism, myocardial infarction/unstable angina, cardiovascular death [including sudden cardiac death], hospitalization for heart failure, or other cardiovascular event requiring hospitalization)	
4. Stroke/TIA or systemic embolism	5. Myocardial infarction/unstable angina
6. Heart failure requiring hospitalization or other cardiovascular event requiring hospitalization	
7. Major bleeding (ISTH criteria^b^)	8. Clinically significant bleeding
9. Major bleeding or clinically significant bleeding	10. Cardiovascular death
11. Other causes of death	12. Device‐related complications
13. Invasive cardiac interventions (surgery, catheter‐based treatments, pacemaker implantation, etc.)	
14. If patients refused implantation, reasons for ICD/CRT‐D/WCD implantation refusal (1. Patient does not want risk associated with implantation, 2. Patient does not believe in benefit of ICD/CRT‐D/WCD, 3 Patient unable to pay for device, or 4 Other reasons)	
Change in the following from the time of enrollment to 1 year (WCD cases: at the time of WCD removal and 12 months after removal):	
1. NYHA (New York Heart Association) functional classification, Clinical Frailty Scale	
2. Echocardiographic measures	
3. Hemoglobin, hematocrit, creatinine, NT‐proBNP or BNP	
4. Nutritional status markers (serum albumin concentration, white blood cell count [peripheral blood lymphocyte count], total cholesterol, C‐reactive protein)	

Abbreviations: BNP, brain natriuretic peptide; CRT‐D, cardiac resynchronization therapy defibrillator; CRT‐P, cardiac resynchronization therapy pacemaker; ICD, implantable cardioverter defibrillator; NT‐proBNP, N‐terminal pro‐brain natriuretic peptide; TIA, transient ischemic attack; VF, ventricular fibrillation; VT, ventricular tachycardia; WCD, wearable cardioverter defibrillator.

^a^
Sudden death: natural death occurring within 24 h of the onset of acute symptoms or instantaneous death, excluding deaths resulting from external factors.

^b^
The International Society for Thrombosis and Haemostasis (ISTH) defines major bleeding as follows: fatal bleeding, bleeding into a major organ or critical area (e.g., intracranial, retroperitoneal, pericardial, intraspinal, intra‐articular, intraocular bleeding), a decrease in the hemoglobin concentration of 20 g/L or more, or transfusion of at least 2 units of blood.^23^

### Sample size and calculation data

2.5

Last year, the number of new patients wearing WCD or undergoing ICD, CRT‐P, CRT‐D, and S‐ICD implantation at our hospital was approximately 30 cases. Therefore, we expect to register about 60 participants per year at our institution for this study (comprising 50% new device implantation cases and 50% non‐implant cases). We also collected device implantation numbers from each participating medical institution (eight institutions) on a yearly basis through a preliminary survey. We initially set the total achievable target registration number at 651 cases, comprising 50% new device implantation cases and 50% non‐implant cases, over a 1.5‐year registration period. However, due to delayed enrollment from these institutions, we expanded the study to include 23 additional institutions (a total of 31 institutions) and extended the registration period to 1.7 years to reach the target number of cases.

### Statistical analysis

2.6

Continuous variables will be presented as mean ± SD or median (25th, 75th percentile) values and categorical variables as the number (%) of patients. Between‐group differences in continuous variables will be analyzed by unpaired *t*‐test or Mann–Whitney U‐test, and between‐group differences in categorical variables will be analyzed by chi‐squared or Fisher's exact test. Serial changes in NYHA, Clinical Frailty Scale, Echocardiographic parameters, and biomarkers will be evaluated by paired *t*‐test. We will examine device introduction rates, especially focusing on the ICD (CRT‐D) implantation as primary prevention, and compare patient characteristics between the ICD/CRT‐D group and non‐ICD (no device/CRT‐P) group. We will investigate the distribution of reasons for ICD/CRT‐D/WCD implantation refusal. Patients eligible for a WCD indication, whether they are using a WCD or not, undergo evaluation for primary prevention ICD eligibility within the first 3 months after registration. If they meet the primary prevention ICD criteria at 3 months after registration, they are categorized as those eligible for ICD primary prevention indication. However, a subset of patients does not meet these criteria and is categorized as the “no ICD indication” group. We expect that most patients will fall into this “no ICD indication” group, and we will investigate and clarify the characteristics of these patients among those eligible for a WCD indication.

Clinical events, such as VT/VF and sudden death, and cardiovascular events, for each group will be reported as percentages of the total population and annual frequencies per person‐year. Additionally, we will utilize the Kaplan–Meier method to calculate the cumulative event rates of clinical events, particularly focusing on VT/VF and sudden death, in the ICD/CRT‐D group, the non‐ICD (no device/CRT‐P) group among patients eligible for primary prevention, and compared these two groups using the log‐rank test. We will conduct Cox proportional hazards analysis to estimate hazard ratios (HRs) and 95% confidence intervals (CIs) for factors related to clinical events. Since the cardiovascular event rate is expected to provide sufficient data for multivariate analysis, we will conduct multivariate analysis to calculate the HR and 95% CI of the non‐ICD (no device/CRT‐P) group relative to the ICD/CRT‐D group in primary prevention for cardiovascular events by adjusting for clinically relevant factors. Based on the HINODE study, the annual occurrence rate of appropriate therapy for VT/VF with heart devices was approximately 6%. The all‐cause mortality rate for the group that did not have an ICD implanted (non‐device and pacing cohorts) was in the range of 8% (over the entire observation period).^17^ In the MADIT‐RIT Trial, the rate of appropriate ICD operation was also above 6%.^24^ In the MADIT II Trial, the rate of sudden cardiac death was approximately 10% in the non‐ICD group and less than 4% in the implanted ICD group, respectively.^15^, ^25^ Considering the low incidence of VT/VF and sudden death in primary prevention (approximately 5%–10%), the limited number of events may render multivariate Cox proportional hazards analysis impractical. Therefore, the propensity score model will be developed using selected variables according to clinical relevance. We will again draw the Kaplan–Meier method along with HR and 95% CI for VT/VF and sudden death for the propensity matched non‐ICD patient group compared with the propensity matched ICD patient group in primary prevention. As such, the results of elected patients after propensity score matching, along with all cohorts, along will be presented in the main text. For other groups, like those eligible for secondary prevention ICD and WCD, we plan to conduct the most comprehensive adjustment analysis possible, considering that the adjustable variables may change with the increasing number of cases.

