## INTRODUCTION

1

The effectiveness of implantable cardioverter defibrillator (ICD) has been well established for both secondary prevention who experienced ventricular fibrillation/ventricular tachycardia (VF/VT), and primary prevention of sudden cardiac death (SCD) in patients with reduced left ventricular ejection fraction (HFrEF). Guidelines from organizations such as the Japanese Circulation Society (JCS), the American Heart Association (AHA), the American College of Cardiology (ACC), the Heart Rhythm Society (HRS), and the European Society of Cardiology (ESC) recommend ICD implantation at class IIa or higher for eligible patients.^1^, ^2^, ^3^ Additionally, for HFrEF patients with a wide QRS on their electrocardiogram and left ventricular ejection fraction (LVEF) less than 35%, the prognostic impact of cardiac resynchronization therapy pacemaker (CRT‐P) and CRT defibrillator (CRT‐D) has become evident^4^, ^5^, ^6^, leading to similar recommendations of class IIa or higher for implantation as outlined in the guidelines of organizations such as JCS, AHA, ACC, the Heart Failure Society of America (HFSA), and ESC.^1^, ^7^, ^8^

Nevertheless, underuse of ICD has been reported especially in Asia including Japan.^9^, ^10^ Several factors contribute to this underutilization, including physicians' awareness, patients' consciousness, and various social factors, such as those associated with aging and economic considerations in Japan.^11^, ^12^, ^13^, ^14^, ^15^, ^16^ However, in recent years, studies undertaken in Japan, such as the HINODE trial, have shown mortality rates and rates of ventricular arrhythmias as high as those in Western countries.^17^ It has attracted attention to the potential significance of ICD/CRT‐D implantation as a primary prevention in Japan.

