### Study design and setting

2.1

The study will be based on TRANSITION JAPAN‐ICD/WCD, a large‐scale, multicenter, prospective registry including three types of HFrEF patients eligible for ICD for primary or secondary prevention of SCD, or WCD in Japan. Enrollment began on April 1, 2023, and the inclusion is planned to end on December 31, 2024, with all patients enrolled being followed up for at least 1 year (with the final follow‐up occurring on or before December 31, 2025). 31 institutions in Japan are participating in the registration (supplemental Figure S1). A flow diagram illustrating the overall follow‐up period and data analysis for the TRANSITION JAPAN‐ICD/WCD study is presented in Figure 1.

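### The analyses in section 2.6 take no account of hospital, although the primary endpoint is a treatment decision that plausibly varies across 31 sites of unequal size

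*Protocol article*

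**What the plan says.** Section 2.1 of the protocol article states that "31 institutions in Japan are participating in the registration". The primary endpoint (section 2.4, Table 4) is the rate of device implantation.

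Section 2.6 summarises categorical variables as number and percentage, and says that between-group differences in them "will be analyzed by chi‐squared or Fisher's exact test". Continuous variables get t-tests or Mann–Whitney tests. For clinical events in primary prevention, the ICD/CRT-D and non-ICD groups get Kaplan–Meier curves, and the article says the authors "compared these two groups using the log‐rank test". Cox models and a propensity-matched comparison follow. Covariates for both are to be chosen by clinical relevance and are not listed. Confidence intervals are mentioned only for hazard ratios.

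Hospital does not appear in section 2.6 as a stratum, random effect, matching factor or unit of clustering.

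On why devices are underused, the Introduction says: "Several factors contribute to this underutilization, including physicians' awareness". It goes on to patients' attitudes and social factors. On site size, section 2.5 says of the lead hospital that "we expect to register about 60 participants per year at our institution for this study".

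**The concern.** All the named methods, in the form given, treat patients as independent. The primary endpoint is a decision taken by physicians with their patients, and physicians work within hospitals. If implantation habits differ between hospitals, two patients at one site are more alike in device use than two patients at different sites. The registry then carries less information about the rate than 651 independent patients would.

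The comparison of outcomes with and without a device, the second stated purpose, raises a separate question. If hospitals that implant more also have patients at different risk, or give different heart failure care, part of the device hazard ratio may reflect hospital. Patient-level covariates may not capture that.

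**Working it through.** **Inputs from the documents.** Target: "We initially set the total achievable target registration number at 651 cases", planned as "comprising 50% new device implantation cases and 50% non‐implant cases, over a 1.5‐year registration period". Sites: 8 + 23 = 31. Lead site: about 60 patients a year over the extended 1.7-year period, so 60 × 1.7 = 102. Expected VT/VF and sudden death in primary prevention: about 5% to 10% (section 2.6).

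**Assumed inputs.** The article gives no ICC and no per-hospital device rates. ICC values of 0.01 to 0.10 are assumptions. The target of 651 is an achievable number from a survey of device volumes, so there is no precision figure of the plan's own to reproduce.

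**Step 1: simple interval for the rate.** Half-width = 1.96 × √(0.5 × 0.5 / 651) = 3.84 points.

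**Step 2: cluster size.** Equal sites: m = 651 / 31 = 21. With one site of 102, the other 30 average (651 − 102) / 30 = 18.3, and the size-weighted mean is (102² + 30 × 18.3²) / 651 = 31.4.

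**Step 3: design effect.** DE = 1 + (m − 1) × ICC. The half-width is multiplied by √DE.

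| Assumed ICC | DE, equal sites | Half-width | DE, lead site 102 | Half-width |
|---|---|---|---|---|
| 0.01 | 1.2 | 4.2 | 1.3 | 4.4 |
| 0.05 | 2.0 | 5.4 | 2.5 | 6.1 |
| 0.10 | 3.0 | 6.7 | 4.0 | 7.7 |

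Coverage of a nominal 95% simple interval is 2Φ(1.96/√DE) − 1. With equal sites it is about 83% at ICC 0.05 and 74% at ICC 0.10. The effective sample size at ICC 0.05 is 326 with equal sites, or 258 with the large lead site.

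**Step 4: device comparison.** The design effect for a single proportion does not carry over, because much of this comparison is made within hospitals. A simulation with no true device effect used 31 hospitals of 21 patients, an average event risk of 20%, and a pooled two-proportion test at 5% that ignores hospital. Assumed values were an ICC of device use (logit scale) up to 0.20 and a between-hospital SD of log-odds of the event up to 0.5.

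| Hospitals differ in | Type I error | Bias |
|---|---|---|
| device use only, or event risk only | 4.2% to 5.3% | about 0 |
| both, independently | 5.1% to 6.5% | about 0 |
| both, correlation 0.5 | 6.4% to 16.9% | 0.9 to 3.0 points |

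Across these settings the true SD of the estimate was at most 1.07 times the naive standard error.

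**Step 5: events per hospital.** Even if all 651 patients counted, 5% to 10% gives 33 to 65 events for VT/VF and sudden death. Over 31 sites that is 1.1 to 2.1 per hospital, and fewer in the primary-prevention or matched subset.

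**The case against.** The strongest reply is that this is a condensed article and that handling of centre is usually left to a fuller plan. Naming a log-rank test or a Cox model does not rule out stratification or robust variance, and the open covariate lists do not exclude hospital. This partly stands: silence alone would not be a finding. But section 2.6 does set out specific analyses in unstratified, patient-level form, and better-suited forms of the same analyses are readily available.

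Three stronger readings are tempting, and the article does not support them:

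- **Device use is driven by hospital practice.** The Introduction gives physicians' awareness as one of several causes, and three of the four listed refusal reasons concern the patient. Variation by hospital is a reasonable expectation, not a stated fact.
- **The planned intervals are too narrow.** No interval is planned for the primary rate, so the figures above describe any simple interval later attached to it. For hazard ratios, where intervals are planned, widening is small (about 0% to 7% in the simulation).
- **Hospital confounds the device comparison.** This needs hospitals to differ in both device use and event risk, with the two associated. The Discussion also concedes residual confounding in general terms.

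It is also fair that chance may dominate for rare events. With 33 to 65 events in equal groups, SE(log HR) is about 2/√events, so the 95% interval runs a factor of 1.6 to 2.0 either way. Site-stratified or frailty models would be a poor use of so few events.

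**Conclusion.** The point holds in a limited form. For the primary rate, any positive ICC makes a simple binomial interval too narrow. The width should be multiplied by about 1.4 at ICC 0.05 and 1.7 at ICC 0.10 with equal sites, and by about 1.6 and 2.0 with a lead site of 102. These figures rest on assumed ICCs, a 50% rate and the full 651 patients. The figure of 102 is the lead hospital's own expectation, and the article reports that enrolment ran late.

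For the ICD against non-ICD comparison, precision is barely affected. Confounding by hospital is possible but conditional. The simulated bias comes from a binary outcome with assumed hospital differences, so it shows the order of size and is not a prediction for the hazard ratios. A clear change to section 2.6 is worth making, but nothing here invalidates the study.

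**What to change.** In section 2.6:

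1. Report the implantation rate with a 95% CI from site-clustered variance.
2. Fit the Cox models, including the propensity-matched analysis, with site-clustered robust variance. This corrects precision only and does not remove confounding.
3. To address confounding, add a sensitivity analysis with hospital as a random intercept in the propensity model, or with hospital in the Cox model for the more frequent cardiovascular events.
4. Do not require site-stratified or frailty Cox models for VT/VF and sudden death.

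The enrolling hospital is known for every patient, so no new data are needed. The cost is wording and software options. Intervals for the hazard ratios would be slightly wider, and the interval for the rate would widen by as much as the observed clustering warrants.

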### Eligibility and non‐eligibility

2.2

This study focuses on HFrEF patients who meet the criteria for receiving ICD for primary and secondary prevention of SCD and those who meet the criteria for WCD for primary prevention. Participants must be 20 years of age or older at the time of obtaining consent and provide written consent based on their own free will after receiving sufficient explanation regarding participation in this study. Patients eligible for this study will be basically fulfilled with the criteria of class I or IIa for ICD including sub‐cutaneous ICD (*S*‐*ICD*), and WCD as outlined in the JCS guidelines^1^: (1) patients with coronary artery disease (CAD) (≥40 days after myocardial infarction (MI) and at least 90 days after revascularization) or non‐ischemic cardiomyopathy who have NYHA class II or greater symptoms and an LVEF ≤35% despite optimal medical therapy, irrespective of whether they've experienced NSVT (criteria for primary prevention of SCD), (2) CAD or non‐ischemic cardiomyopathy who have NYHA class II or greater symptoms and an LVEF ≤35% accompanied by ventricular fibrillation (VF) or out‐of‐*hospital* cardiac *arrest* requiring electrical shock, sustained VT or unknown syncope, not due to reversible causes (criteria for secondary prevention of SCD), and (3) patients with LVEF ≤35% and HF symptoms of NYHA class II or III, and within 40 days after the onset of acute MI, and are within 90 days after coronary artery bypass or percutaneous coronary intervention, or within 90 days after the acute onset of HF due to a non‐ischemic etiology (WCD criteria). Therefore, this study will also include the patients who have opted not to receive ICD or WCD based on the patients' preference, including those without any cardiac device or those with CRT‐P. The following patients are excluded from this study: (1) those with a life expectancy of less than 12 months, (2) patients with frequent recurrent VT or VF that cannot be controlled with antiarrhythmic drugs or catheter ablation, (3) severe HF patients classified as NYHA class IV, (4) individuals unable to provide consent for the study, and (5) others judged unsuitable as study subjects by the principal researcher.

In short, the target cases for this study are those aged 20 or older with LVEF ≤35% and NYHA class II or higher HF symptoms despite adequate medical therapy, who do not fall under the exclusion criteria mentioned above.

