Date of informed consent Age, gender, height, weight Smoking habits: Current/Former/Never Alcohol consumption: Daily / 2–3 times a week/Never Underlying heart disease (Ischemic cardiomyopathy/non‐ischemic cardiomyopathy [Dilated cardiomyopathy/hypertrophic cardiomyopathy/hypertensive heart disease/others]) NYHA functional classification (I/II/III/IV) Medical history (Diabetes, hypertension, dyslipidemia, ischemic heart disease [History of myocardial infarction/Angina], history of heart failure, chronic obstructive pulmonary disease, history of stroke, peripheral arterial disease) Clinical Frailty Scale: 1–9 Medication History ① Beta‐Blockers: Yes/No ② ACEi/ARB (angiotensin‐converting enzyme inhibitor / angiotensin receptor blocker): Yes/No ③ Mineralocorticoid Receptor Antagonists: Yes/No ④ ARNi (Angiotensin Receptor‐Neprilysin Inhibitor): Yes/No ⑤ SGLT2i (Sodium‐Glucose Cotransporter 2 Inhibitors): Yes/No ⑥ Ivabradine: Yes/No ⑦ Pimobendan: Yes/No ⑧ Digoxin Preparations: Yes/No ⑨ Antiarrhythmics: Sodium Channel Blockers (Procainamide/Disopyramide/Flecainide/Cibenzoline/ Pirmenol/Aprindine/Propafenone), Potassium Channel Blockers (Amiodarone/Sotalol/Bepridil) ⑩ Anticoagulants: Warfarin/Direct Oral Anticoagulants (DOACs) ⑪ Antiplatelet Agents: Yes/No ⑫ Lipid‐Lowering Medications: Yes/No ⑬ Diabetes Medications (excluding SGLT2i): Yes/No History of revascularization (percutaneous coronary intervention, coronary artery bypass grafting) Presence of atrial fibrillation/flutter (paroxysmal/persistent/permanent) Presence of NSVT (≥5 beats) History of ablation therapy for NSVT/VT History of cancer (gastrointestinal/lung/other) Dialysis (yes/no) Echocardiogram (LVEDV [mL], LVESV [mL], LVDd [mm], LVDs [mm], LAD [mm], LVEF [%], presence of moderate or severe valvular disease [MR, TR, AR, AS]) Electrocardiogram (heart rate, rhythm, QRS duration [ms], presence of ventricular pacing) Laboratory data (NTproBNP [pg/mL] or BNP [pg/mL], WBC [×10^9^/L], lymphocyte count [×10^9^/L], Hb [g/dL], Plt [×10^9^/L], BUN [mg/dL], Cr [mg/dL], eGFR [mL/min/1.73 m^2^], UA [mg/dL], AST [U/L], ALT [U/L], rGTP [U/L], Tcho [mg/dL], Na [mmol/L], K [mmol/L], TP [g/dL], Alb [g/dL], CRP [mg/dL]) Confirmation of performance only Signal‐averaged electrocardiogram (present/absent) Holter monitoring (present/absent) Cardiac MRI (present/absent)
(2) At 12 Months (±3 Months) (WCD indication group: at 3 Months corresponding to the time of WCD removal phase and 12 months after removal phase)

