NYHA functional classification (I / II / III / IV) Echocardiogram (LVEDV [mL], LVESV [mL], LVDd [mm], LVDs [mm], LAD [mm], LVEF [%], presence of moderate or severe valvular disease [MR, TR, AR, AS]) Electrocardiogram (heart rate, rhythm, QRS duration [ms], presence of ventricular pacing) Labotatory data (NTproBNP [pg/mL] or BNP [pg/mL], WBC [×10^9^/L], lymphocyte count [×10^9^/L], Hb [g/dL], Plt [×10^9^/L], BUN [mg/dL], Cr [mg/dL], eGFR [mL/min/1.73 m^2^], UA [mg/dL], AST [U/L], ALT [U/L], rGTP [U/L], Tcho [mg/dL], Na [mmol/L], K [mmol/L], TP [g/dL], Alb [g/dL], CRP [mg/dL])

Abbreviations: AR, aortic regurgitation; AS, aortic stenosis; Alb, albumin; ALT, alanine aminotransferase; AST, aspartate aminotransferase; BNP, brain natriuretic peptide; BUN, blood urea nitrogen; CRP, C‐reactive protein; Cr, creatinine; eGFR, estimated glomerular filtration rate; Hb, hemoglobin; LAD, left atrial diameter; LVDd, left ventricular diastolic diameter; LVDs, left ventricular systolic diameter; LVEF, left ventricular ejection fraction; LVEDV, left ventricular end‐diastolic volume; LVESV, left ventricular end‐systolic volume; end‐systolic volume; MR, mitral regurgitation; NT‐proBNP, N‐terminal pro‐brain natriuretic peptide; NSVT, Non‐sustained ventricular tachycardia; NYHA, New York Heart Association; Plt, platelet; rGTP, γ‐glutamyltranspeptidase; Tcho, total cholesterol; TP, total protein; TR, tricuspid regurgitation; UA, uric acid; VT, ventricular tachycardia; WBC, white cell count.

**TABLE 3 joa313028-tbl-0003:** Observation items.

Observation Items (To be observed for a minimum of 12 months from the date of registration)

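### One paired t-test is fixed for every serial change, and NT-proBNP and BNP share one change endpoint with no same-assay rule (minor; secondary endpoints only)

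*Protocol article*

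**What the plan says.** The Statistical analysis section (2.6) names one method for change over time: "Serial changes in NYHA, Clinical Frailty Scale, Echocardiographic parameters, and biomarkers will be evaluated by paired" t-test. Earlier in the same section the plan provides for non-normal data in other settings. It says "Continuous variables will be presented as mean ± SD or median (25th, 75th percentile) values", and it allows the Mann–Whitney test for between-group comparisons. No such choice is given for change within patients.

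The variables covered differ in kind:

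- **Ordinal scales.** Table 2 records "NYHA functional classification (I/II/III/IV") and "Clinical Frailty Scale: 1–9".
- **Natriuretic peptide.** The registration list has "NTproBNP [pg/mL] or BNP [pg/mL"]. The follow-up list repeats the alternative: "NTproBNP [pg/mL] or BNP [pg/mL], WBC". Neither list says that the follow-up assay must match the one used at registration.
- **Echocardiography.** The items include volumes, diameters and LVEF, and also the presence of moderate or severe valvular disease.

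Table 4 makes these changes secondary endpoints. One is the change in "Hemoglobin, hematocrit, creatinine, NT‐proBNP or BNP", and CRP is among the nutritional markers. The article gives no standard deviation, significance level or power for any of these tests.

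**The concern.** The paired t-test compares mean differences. For a strongly right-skewed marker measured in pg/mL, a few patients with very high values dominate both the mean difference and its standard error. A proportional fall shared by most patients can then be missed.

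The two peptides raise a separate problem. They are different analytes on different scales. Averaging pg/mL differences over patients measured with one or the other gives a number that belongs to neither. If a patient has one assay at registration and the other at follow-up, the subtraction records the change of assay as well as any change in the patient. With 31 institutions contributing, the plan should rule this out.

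Two smaller matters follow from the same sentence. A mean change in NYHA class does not show how many patients improved or worsened. A paired t-test also does not suit the presence or absence of valvular disease.

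**Working it through.** The documents give no figure for these tests to reproduce. The target of 651 is a recruitment number built from device counts, not from power. Everything below except 651 is therefore an assumption: two-sided 5% level, log-normal biomarker, equal log-SD s at both visits, within-patient correlation r, geometric mean ratio g, and n complete pairs.

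**1. Power, raw against log scale**

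In units of the baseline mean, the raw difference has mean 1 − g and variance (e^{s²} − 1)(1 + g²) − 2g(e^{r·s²} − 1). The log difference has mean ln g and SD s·√(2(1 − r)). Power is approximately Φ(√n × |mean|/SD − 1.96).

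Worked case: n = 325 (about half of 651), s = 1.0, r = 0.7, g = 0.85.

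- Raw: variance = 1.7183 × 1.7225 − 1.70 × 1.0138 = 1.236, SD 1.112. √325 × 0.15/1.112 = 2.43, so power is about 68% (simulated 71%).
- Log: SD = √0.6 = 0.775. √325 × 0.1625/0.775 = 3.78, so power is about 97% (simulated 97%).

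Simulated power over a range of assumptions:

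| Pairs | log-SD | r | g | Raw t | Log t | Loss (points) |
|---|---|---|---|---|---|---|
| 550 | 0.8 | 0.7 | 0.80 | 100% | 100% | 0 |
| 550 | 1.0 | 0.6 | 0.80 | 97% | 100% | 3 |
| 550 | 0.8 | 0.7 | 0.90 | 86% | 98% | 12 |
| 550 | 1.2 | 0.6 | 0.80 | 82% | 100% | 18 |
| 200 | 1.0 | 0.6 | 0.80 | 67–70% | 93–94% | about 25 |
| 325 | 1.0 | 0.7 | 0.85 | 71% | 97% | 26 |
| 200 | 1.2 | 0.6 | 0.80 | 44–46% | 83–85% | about 40 |
| 550 | 1.3 | 0.7 | 0.85 | 54% | 97% | 43 |
| 325 | 1.3 | 0.7 | 0.85 | 36% | 82% | 46 |

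The last row is the largest gap found. With no true change and one assay, the raw test's false-positive rate stayed between 3.6% and 5.8%. On a single assay the harm is therefore lost power and a mean driven by extremes, not a false signal.

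**2. Switching assay, no true change**

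Suppose a share p of patients has NT-proBNP at registration and BNP at follow-up, with an assumed ratio of 6:1. The raw mean then falls by p × 5/6 and the geometric mean ratio becomes e^{−p·ln 6}. For p = 2%, 5% and 10% the raw mean falls by 1.7%, 4.2% and 8.3%, and the ratio is 0.96, 0.91 and 0.84.

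Simulated false positives with 550 pairs, log-SD 1.0, r = 0.7:

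| Share switching | Raw t | Log t | Wilcoxon signed-rank |
|---|---|---|---|
| 2% | 7% | 18% | 9% |
| 5% | 12% | 68% | 22% |
| 10% | 39% | 99.5% | 68% |

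With r = 0.6 the raw figures for 5% and 10% are about 12% and 32%. Taking logs without a same-assay rule makes the problem worse, so the two changes must be made together.

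**3. NYHA**

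Patients enter essentially in class II or III: class II or higher is required, and "severe HF patients classified as NYHA class IV" are excluded. With one-class moves only (15% up and 25% down, 325 pairs), the paired t-test and signed-rank test had 81.1% and 80.9% power. With 15% moving each way, both rejected in about 5% of runs.

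**The case against.** The strongest reply is that the article does not say the biomarkers are analysed untransformed. A paired t-test on log values is still a paired t-test, and a condensed article may leave the transformation to the full protocol or analysis plan. Likewise, no text says that the two peptides will be pooled or that any patient will change assay. This stands as a limit on the claim: raw analysis is inferred, and switching is permitted rather than described. It does not remove the point. The article names a single test for all serial changes while allowing rank methods elsewhere, and it defines one endpoint from either peptide.

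A reader might infer more than the documents support in three ways:

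- **That the biomarker endpoints would be under-powered.** No power target, spread or effect is stated, and with 550 pairs and moderate skew the loss can be nil.
- **That a t-test on NYHA gives wrong error rates.** The calculation shows no material difference from the signed-rank test. The objection there concerns what a mean class change conveys.
- **That NYHA and frailty results would be too favourable because patients who die leave the paired test.** Nothing allows this to be quantified, and death from any cause is reported as its own secondary endpoint. The non-ICD mortality the article cites is about 8% over that study's whole observation period. Ranking death as the worst outcome would answer a different question, so it is an option and not a correction.

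**Conclusion.** The point holds in limited form and is minor. The article fixes one test for variables of different kinds and leaves the natriuretic peptide endpoint open to mixing two assays.

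If values are analysed untransformed, the loss of power on skewed biomarkers runs from none to somewhat over 40 points in the scenarios tried. The size depends on assumed log-SD (0.8 to 1.3), correlation (0.5 to 0.7), effect (a fall of 10% to 20%) and number of pairs (150 to 550). If assays are mixed within patients in one direction, false positives can rise well above 5%. That result rests on the assumed 6:1 ratio and switching share.

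These are secondary endpoints of an observational registry with no stated power. The primary endpoint, the device implantation rate, and the survival analyses are unaffected.

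**What to change.** Reword the serial-change sentence and add a pairing rule:

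1. Analyse NT-proBNP, BNP and CRP on the log scale and report geometric mean ratios with confidence intervals. Analyse each peptide separately, using only pairs measured with the same assay.
2. Report NYHA and Clinical Frailty Scale changes with shift tables and a Wilcoxon signed-rank test, for interpretability and not for power.
3. Keep the paired t-test for continuous echocardiographic measures. Use a paired categorical test such as McNemar's for the presence of moderate or severe valvular disease.
4. State that each change describes patients alive and assessed at the visit.

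This changes analysis wording only and needs no new patients, visits or tests. The cost is smaller numbers for each peptide and the loss of any pair with mismatched assays.
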